## **Sample size**

This is based upon the calculations for the primary outcome of the trial. A separate sample size calculation for the HRQL study has not been performed.

## **Statistical analysis plan**

Data will be scored according to the algorithms described in the EORTC QLQ-C30 scoring manual . All scales and single items are scored on categorical scales and linearly transformed to 0-100 scales where: (a) a high score for a symptom scale or item represents a high level of symptoms or problems, and (b) a high score for a functional scale represents a high or health level of functioning and a high score for the global health status/HRQL represents high QL. Groups of patients will be compared at agreed time points and overall for differences in these parameters. The treatment groups will be compared at the individual time points with appropriate adjustments being made for multiple comparisons. Because of the longitudinal nature of the data, an analysis that takes into account the repeated measures is also needed. A generalised linear modelling approach will be adopted. This will allow the appropriate error distribution to be used and will enable the analysis to take account of important prognostic factors.

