  - Glomerular filtration rate (GFR) assessed by EDTA clearance to be  $> 40mL/min$  (or estimated by Cockcroft-Gault formula to be  $> 60 mL/min$ ) (Appendix II) (please note dose reduction for GFR 40 to 50ml/min, see p43).
12. Patients who are fit to receive all protocol treatment.
13. Patients who are able and willing to administer capecitabine.
14. Patients who are of child bearing age are willing to use contraception.
15. Patients who have completed baseline quality of life questionnaires (Appendices III and IV).
16. Patients who have provided written informed consent prior to randomisation.

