#### **Cost per QALY**

Differences between the two groups in terms of resources utilised and QALYs will be determined and a cost per QALY estimate produced.

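### The HRQL comparisons at each time point name only a multiplicity adjustment; the same-scale baseline score, which must be collected before randomisation, should be named as a covariate

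*Protocol*

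**What the plan says.** Section 14 of the protocol has its own subsection on the statistical analysis of HRQL, and it describes two kinds of comparison.

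- At single time points: "The treatment groups will be compared at the individual time points with appropriate adjustments being made for multiple comparisons".
- Over time: "Because of the longitudinal nature of the data, an analysis that takes into account the repeated measures is also needed". The next sentences add "A generalised linear modelling approach will be adopted" and say that this "will enable the analysis to take account of important prognostic factors". The factors are not listed. The text does not make clear whether the modelling approach also covers the single time points or only the repeated-measures analysis.

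The baseline score is named in neither place, as a covariate or otherwise.

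The baseline itself is secured elsewhere. Section 4.1.1, item 15, admits only "Patients who have completed baseline quality of life questionnaires". Section 4.2 lists QLQ-C30, QLQ-OES18 and DLQI among the procedures due in the week before randomisation. Section 4.3 makes a completed baseline questionnaire a condition of randomisation, and section 14 repeats the timing.

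On size, section 14 says: "A separate sample size calculation for the HRQL study has not been performed". HRQL relies on the 420 patients set for overall survival in section 12.3. Section 12.5 announces a detailed statistical analysis plan, which is not at hand.

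**The concern.** The earlier score of the same patient on the same scale is usually among the best predictors of a later score. This trial requires that score from everyone before allocation, yet the stated time-point comparison names a correction for multiplicity and leaves out the standard covariate.

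The HRQL aims in section 14 are directional. They expect better physical and role function, fatigue, dysphagia and eating restrictions after treatment, and worse dyspnoea, rash and diarrhoea during it. No sample size supports these aims, the number of responders will fall with deaths and non-completion, and the multiplicity correction takes further power. Precision available at no cost is therefore worth having.

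A second consideration is that a chance baseline difference, for example in dysphagia, passes in part into an unadjusted follow-up difference. If covariates are settled only after data have been seen, the HRQL conclusions become open to dispute.

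**Working it through.** **1. The plan's own figure.** The protocol states no HRQL power or sample size. The figure that HRQL relies on is 420 patients and 269 events for overall survival (section 12.3: 2-year survival 35% versus 47.5%, 80% power, two-sided 5%, 3 years of recruitment plus 1 year of follow-up).

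- HR = ln(0.475)/ln(0.35) = 0.709.
- Events needed: 266 (Schoenfeld) or 271 (Freedman).
- With exponential survival and uniform accrual, the mean event probability is 0.643, so 420 × 0.643 gives about 270 events.

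The stated figure reproduces. No HRQL figure exists to be shown wrong.

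**2. Variance with and without baseline.** For n per arm and standard deviation SD at a time point, the arm difference has variance

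- unadjusted: 2·SD²/n;
- adjusted for the same-scale baseline: 2·SD²·(1 - rho²)/n.

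The unadjusted variance is 1/(1 - rho²) times the adjusted one. rho is not in the documents; 0.3 to 0.7 is an assumed range.

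| rho | 1 - rho² | variance ratio | 210 per arm act like |
|---|---|---|---|
| 0.3 | 0.91 | 1.10 | 231 |
| 0.5 | 0.75 | 1.33 | 280 |
| 0.7 | 0.51 | 1.96 | 412 |

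**3. What that means for power.** Power = Phi(difference/SE - 1.96), before any multiplicity correction.

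- A comparison with 80% power unadjusted has difference/SE of about 2.80. Dividing by sqrt(1 - rho²) gives 83.6% at rho 0.3, 89.9% at 0.5 and 93.8% at 0.6.
- Assumed difference of 0.3 SD, 210 per arm: 86.7% unadjusted; 89.7%, 94.4% and 99.0% at rho 0.3, 0.5 and 0.7.
- Same difference with 100 per arm still responding (assumed): 56.4% unadjusted; 60.4%, 68.8% and 84.4%.

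**4. A worked week-24 example.** Exponential survival at 35% by 2 years gives 0.35^(24/104) = 0.785 alive. With 80% completion (assumed), 210 × 0.785 × 0.80 is about 132 per arm. Take SD 30, a 10-point difference and rho 0.5 (all assumed).

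- Unadjusted: SE = 30 × sqrt(2/132) = 3.69; 10/3.69 - 1.96 = 0.75; power 77.3%.
- Adjusted: SE = 3.69 × sqrt(0.75) = 3.20; 10/3.20 - 1.96 = 1.17; power 87.8%.

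**5. Chance imbalance.** With 210 per arm, the baseline mean difference has SE = sqrt(2/210) = 0.098 SD. An imbalance of 1.96 SE (0.19 SD) would move an unadjusted follow-up estimate by rho × 0.19, that is 0.06, 0.10 or 0.13 SD at rho 0.3, 0.5 or 0.7. Over repeated randomisations this averages to zero. It is an error conditional on the imbalance and not a bias of the method.

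**The case against.** The strongest reply is that this is silence, and that a covariate list for a secondary outcome normally belongs in the statistical analysis plan. Section 14 never calls the comparisons unadjusted or based on raw scores. It adopts a modelling approach with prognostic covariates, among which a baseline score would fit, and a repeated-measures model could also take baseline as its first measurement. Valid tests and intervals already allow for chance imbalance. The size of the gain rests wholly on assumed values and will differ by scale. DLQI was added for a rash that cetuximab causes, and a pre-treatment score may predict it poorly.

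Most of this stands. A reader might infer that the protocol commits to an unadjusted analysis, or that precision has already been lost; the text supports neither, because baseline is neither named nor excluded. A reader might also infer biased HRQL estimates, which randomisation rules out on average.

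What the reply does not remove is that section 14 sets out the time-point comparison separately and names one adjustment for it. An analysis that followed the sentence literally would omit baseline. A better method is available from data that must already be collected, so the point goes beyond an unlisted covariate.

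One might extend the point to health economics, where section 15 says: "Differences between the two groups in terms of resources utilised and QALYs will be determined and a cost per QALY estimate produced". The documents do not support that. The sentence does not commit to a raw difference. Section 5.1 asks for EQ-5D before treatment, in addition to the pre-randomisation procedures, and section 6.1 allows up to two weeks between randomisation and the start of treatment. In an open trial, baseline EQ-5D may therefore be recorded after allocation is known.

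**Conclusion.** The point holds as a low-severity improvement. As written, the time-point HRQL comparisons name adjustment for multiplicity only, and the same-scale baseline score is named neither there nor for the repeated-measures model. Analysed literally, the time-point comparisons would have a variance about 1.10, 1.33 or 1.96 times that of a baseline-adjusted comparison, for assumed rho of 0.3, 0.5 or 0.7. The power figures rest further on assumed differences, SD and completion, none of which the documents give.

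There is no bias on average, no stated figure is wrong, and the overall survival analysis, the Stage 1 decision and the sample size are untouched. The unseen analysis plan may already name the baseline score. In that case the remaining task is to bring section 14 into line with it.

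**What to change.** In section 14, state that the arms are compared at each time point, and in the repeated-measures model, with the baseline score of the same scale as a covariate plus the minimisation factors. In the longitudinal model, add baseline-by-time terms so that the influence of baseline can weaken over follow-up. Say explicitly that the modelling approach covers the single time points as well. Carry the same wording into the statistical analysis plan before any comparison by arm is seen.

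No change to section 15 is required on this point. If baseline EQ-5D is used as a covariate for QALYs, restrict that use to values recorded before randomisation.

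The cost is a few sentences. No new data, visits or patients are needed.

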## 15. HEALTH ECONOMICS

### **Cost-utility analysis of cetuximab in addition to chemoradiation in oesophageal cancer**

**Aim:** The aim of this sub study is to assess the cost-utility of cetuximab in addition to chemoradiation in the treatment of patients with oesophageal cancer.

**Perspective:** The perspective to be employed is that of the UK National Health Service, but with consideration also given to patient and family related costs.

**Design:** The cost-utility analysis will involve a comparison of the additional costs associated with the use of cetuximab in the treatment regimen  $\pm$  any changes in resources utilised elsewhere.

#### **Costs and resource utilization**

Costs of cetuximab will be based on discussions with clinicians and finance staff\*, while other healthcare resources utilised by patients during the study period will be collected via the healthcare resource utilisation log administered during treatment and at follow-up. At each of the 3-4 weekly visits, patients will be asked to indicate whether they have had any contacts with their GP, practice nurse, community nurse or attended hospital either as an outpatient or in-patient. They will be asked whether the contact was connected to their condition or for any other purpose. The involvement of others in providing transport and/or support will also be logged. In addition, they will be asked to indicate the medication they have been taking during the 3-4 week period. Consultations with healthcare professionals will be costed using published sources of unit costs and healthcare resources utilised will be added to the respective treatment costs in each arm.

#### **Quality adjusted life years (QALYs)**

QALYs will be derived from survival data generated during the second stage of the trial and from the EQ-5D# (Appendix VIII) scores collected at baseline, during treatment and at follow-up. The patient diary will also be used to collect additional data.

#### **Cost per QALY**

Differences between the two groups in terms of resources utilised and QALYs will be determined and a cost per QALY estimate produced.

#### **Sensitivity analysis**

A probabilistic sensitivity analysis will be undertaken and a cost-effectiveness acceptability curve produced. In addition a series of one-way sensitivity analyses will be undertaken to assess the robustness of the estimate to changes in costs, resources utilised, utility scores and QALYs.

\*The cost will be assessed despite being made available for the trial by Merck KGaA

#EQ-5D is generally accepted as appropriate for determination of QALYs

## 16. T-SCOPE (TRANSLATIONAL LABORATORY RESEARCH)

The SCOPE 1 trial is an excellent opportunity to prospectively collect EUS biopsy samples for a range of translational research. Translational studies would look at a number of key areas;

- Determine to what extent EGFR status could predict the response to cetuximab.
- Establish a correlation between EGFR inhibition and DNA repair.
- Determine the effect of cetuximab on overall DNA repair.

Translational studies would also be able to look at other aspects of oesophageal cancer and the effect of CRT, and include histological and biochemical investigations. These could include:

- Identify molecular predictors of outcome independent of tumour staging for patients with oesophageal cancer undergoing CRT.
- Determine DNA damage caused by CRT and link this to the cell cycle and related protein expression / synthesis and pathways.
- Describe the relationship between tumour cell density and composition of the interstitium to determine the interstitial diffusion coefficient of therapeutic agents
- Provide more detailed histological characterization of this type of tumour.

Blood samples will allow both heterozygosity studies to be carried out and biochemical markers to be investigated.

Details of these translational studies will be contained within separate proposals to reflect the expertise of the group carrying out this research. The WCTU will co-ordinate these activities which will include transport, storage and distribution of the samples. The WCTU will ensure data is confidential and specific information is released only at times agreed by the IDMC.

The main protocol covers pre and post treatment paraffin embedded biopsy samples. A matched blood sample will also be collected and stored. **See Appendix IX for more detail about sample collection procedures.** Paraffin embedded biopsy samples are also requested if biopsy is taken as a result of clinical decision to investigate disease progression during follow up. This does not exclude the possibility of fresh frozen sample, or sample collected into fixation solution being added. This would constitute a separate proposal and ethics carried out for a sub-set of patients for specific measures providing the expected number of samples will give sufficient power to provide statistical significance and are supported by sufficient funding.

A separate section is included in the consent form for the storage of paraffin blocks and the collection and storage of blood samples for translational research.

## **17. QUALITY ASSURANCE OF RADIOTHERAPY**

For the SCOPE 1 trial there is a Quality Assurance of Radiotherapy sub-study. This will consist of the following:

### **17.1 Educational component**

An educational CD ROM is being distributed to all investigators. This CD ROM includes three example cases, each of which consist of a clinical summary, CT slice data, outlines and Radiotherapy plan information. GUINNESS software is provided for viewing the CT, outline and planning data.

A radiotherapy treatment planning and delivery protocol has been written and is supplied in hard copy and electronically on the CD ROM.

### **17.2 Test Case**

All clinical and radiation oncologists participating in the trial are required to outline a test case. All planning departments are required to plan this test case. This would usually be carried out on the outline completed by the Principal Investigator. The CT data set is included on the educational CD ROM.

All centres and Investigators must have a 'Pass' for the planned test case before entering patients into the trial.

### **17.3 Questionnaires**

Centres are required to complete the following questionnaires:

- National QA for Clinical Trials baseline questionnaire if this has not already been completed
- SCOPE 1 specific questionnaire

### **17.4 Equipment validation**

A visit by the QA team to validate dosimetry for this body region if not already carried out for the INCH or CONVERT trial.

### **17.5 Patient cases**

On trial, centres are required to provide a full dataset of images, structures, plan and doses for each patient. The first clinical case from each investigator, a 10% sample and those with noted major deviations from the protocol will be analysed real time. However centres are to continue with planned treatment and not to wait for a response from the QA team.

The data from the QA RT programme will be analysed separately from the main trial. The participants will be notified of any major deviations.

## **18. TRIAL COMMITTEES AND TRIAL MANAGEMENT ARRANGEMENTS**

The Trial Management Group (TMG) co-ordinates and manages the trial's day-to-day activities. The TMG is comprised of the Chief Investigator, other Co-Investigators and members of the WCTU.

The data will be reviewed (periodically) by an Independent Data Monitoring Committee (IDMC) as described in the trial specific IDMC charter, consisting of at least two Clinicians who are not responsible for patients entered into the trial and an independent Statistician. The IDMC will be asked to recommend whether the accumulated data from the trial, together with results from other relevant trials, justifies continuing recruitment of further patients. A decision to discontinue recruitment, in all patients or in selected subgroups will be made only if the result is likely to convince a broad range of clinicians including trial Investigators and the general clinical community. If a decision is made to continue, the IDMC will advise on the frequency of future reviews of the data on the basis of accrual and event rates. The IDMC will make confidential recommendations to the Trial Steering Committee (TSC).

The role of the TSC is to act on behalf of the sponsor and funder, to provide overall supervision for the trial, to ensure that it is conducted in accordance with GCP, and to provide advice through its independent chairman. This independent committee will review the recommendations from the IDMC and will decide on continuing or stopping the trial, or modifying the protocol.

## APPENDIX I

### WHO Performance status

|   |                                                                                                                    |
|---|--------------------------------------------------------------------------------------------------------------------|
| 0 | Able to carry out normal activity without restriction.                                                             |
| 1 | Restricted in physically strenuous activity but ambulatory and able to carry out light work.                       |
| 2 | Ambulatory and capable of self-care but unable to carry out any work: up and about more than 50% of working hours. |
| 3 | Capable only of limited self-care; confined to bed or chair more than 50% of waking hours.                         |
| 4 | Completely disabled; cannot carry out any self-care; totally confined to bed or chair.                             |

## APPENDIX II

### Renal Function

Cockcroft & Gault formula

$$\text{GFR for males} = \frac{1.23 \times [140 - \text{age}] \times \text{weight (kg)}}{\text{Serum creatinine } (\mu\text{mol/l})}$$

$$\text{GFR for females} = \frac{1.05 \times [140 - \text{age}] \times \text{weight (kg)}}{\text{Serum creatinine } (\mu\text{mol/l})}$$

- A patient with a Cockcroft & Gault estimate of GFR  $\geq 60$  ml/min using the above formula is eligible for the trial.
- Patients with GFR  $< 60$  ml/min should have confirmation by EDTA clearance, other isotopic method or 24hr creatinine clearance and will be eligible if the GFR  $\geq 40$ .
- After start of treatment, if Cockcroft & Gault estimate falls by 25% from baseline to below 50 ml/min, the EDTA should be performed but an appropriate dose modification made according to protocol pending this result

**Treatment modification in the case of any renal toxicity is in section 8.4 of the protocol.**

## APPENDIX III

### WHO grades of hearing impairment

| Grade of impairment                        | Corresponding audiometric ISO value | Performance                                                      | Recommendations                                                                                                           |
|--------------------------------------------|-------------------------------------|------------------------------------------------------------------|---------------------------------------------------------------------------------------------------------------------------|
| 0 – No impairment                          | 25 dB or better (better ear)        | No or very slight hearing problems. Able to hear whispers.       |                                                                                                                           |
| 1 – Slight impairment                      | 26-40 dB (better ear)               | Able to hear and repeat words spoken in normal voice at 1 metre. | Counselling. Hearing aids may be needed.                                                                                  |
| 2 – Moderate impairment                    | 41-60 dB (better ear)               | Able to hear and repeat words spoken in raised voice at 1 metre. | Hearing aids usually recommended.                                                                                         |
| 3 – Severe impairment                      | 61-80 dB (better ear)               | Able to hear some words when shouted into better ear.            | Hearing aids needed. If no hearing aids available, lip-reading and signing should be taught.                              |
| 4 – Profound impairment including deafness | 81 dB or greater (better ear)       | Unable to hear and understand even a shouted voice.              | Hearing aids may help understanding words. Additional rehabilitation needed. Lip-reading and sometimes signing essential. |

Grades 2, 3 and 4 are classified as disabling hearing impairment.

The audiometric iso values are averages of values at 500, 1000, 2000, 4000 Hz.

## **APPENDIX IV**

### **Investigations**

#### **Multi-slice CT scan (within 4 weeks of randomisation)**

Patients should be staged with multi-slice CT to assess the local extent of the primary tumour, the presence of loco-regional lymphadenopathy and distant metastatic disease. A water load is used, dysphagia permitting, to maximise oesophageal and gastric distension. Intravenous contrast should be used and CT scan of the thorax and abdomen acquired at 1.25-2.5mm and reformatted at 5mm for viewing (RCR Guidelines 2006).

#### **Endoscopic Ultrasound (within 4 weeks of randomisation)**

Patients should be staged with endoscopic ultrasound (EUS) to assess the extent of visible and sub-mucosal tumour, infiltration by the primary tumour of surrounding mediastinal structures and the presence and site of site of significant lymphadenopathy. The following will be recorded:

Location of disease and anatomical structures should be described according to the distance in cms from the incisor teeth.

OGD: Proximal and distal tumour extent (cms from the incisor teeth)

Amount of gastric involvement (measurement from oesophago – gastric junction)

EUS: Reference point e.g. top of arch of aorta, tracheal carina

Proximal and distal tumour extent (including submucosal disease)

T stage of tumour

If T4, record involvement of surrounding structures (e.g. right/left parietal pleura, aorta, trachea, diaphragmatic crus etc)

Pathological appearing lymphadenopathy, including distance and station (right/left tracheal, aortopulmonary window, subcarinal, paraoesophageal with relationship to tumour, paracardial, left gastric)

